| **Objective** | To explore the safety, feasibility and efficacy of thrombectomy with sufficient recanalization bridged by intra-arterial cocktail therapy in acute ischemic stroke patients. |
| **Efficacy Outcome** | **Primary outcome：**   1. Proportion of modified Rankin Score (mRS, 0–2) at 90±7 days after randomization.   **Secondary outcomes：**   1. Proportion of mRS (0–1) at 90±7 days after randomization; 2. Occurrence of early neurological improvement within 48±12 hours. |
| **Safety Outcome** | Occurrence of symptomatic intracranial haemorrhage within 48±12 hours. |
| **Trial Design** | This is a prospective, single arm, open label, blinded endpoint, and single-centre trial. Follow-up will be performed at baseline, 48±12 hours, 10±2 days, and 90±7 days after randomization. All the investigators and outcome assessors will be masked to the allocation assignment and follow-up. |
| **Trial Population** | Acute anterior circulation large vessel occlusion patients with successful recanalization after endovascular treatment |
| **Sample Size** | 30 |
| **Inclusion criteria** | 1. Age ≥18 years. 2. Patients who presented with acute ischemic stroke and a large vessel occlusion in the anterior circulation and met the criteria of mechanical thrombectomy. 3. Sufficient recanalization (mTICI 2b-3) within 7 hours of stroke onset. 4. Signed informed consent. |
| **Exclusion criteria** | **Excluded**   1. insufficient recanalization (mTICI < 2a) after endovascular treatment; 2. Haemorrhagic stroke: cerebral haemorrhage, subarachnoid haemorrhage. 3. Coagulation disorders, systematic haemorrhagic tendency, thrombocytopenia （ <100000/mm3）. 4. Severe hepatic or renal dysfunction, increase in ALT or AST (more than 2 times of upper limit of normal value), increase in serum creatinine (more than 1.5 times of upper limit of normal value) or requiring dialysis. 5. Severe uncontrolled hypertension (systolic blood pressure over 200mmHg or diastolic blood pressure over 110 mmHg). 6. Patients with contraindication or allergic to any ingredient of drugs in our study. 7. Patients not suitable for the study considered by researcher. |
| **Trial Cycle** | All included patients will be followed up at 48 ± 12 hours, 10 ± 2 days, and 90 ± 7 days after enrolment. |
| **Treatment Regimens** | All enrolled patients will receive intra-arterial administration of argatroban (0.2-0.3 mg/min), dexamethasone (0.1 mg/min) and edaravone (0.3 mg/min) for 30 to 60 minutes after the end of thrombectomy. |
| **Procedure** | **Screening period:** On day 0 (baseline period), it is necessary to complete enrolment screening, and collect demographic characteristics, medical history (including history of hypertension, diabetes and drug treatment history), brain imaging (computer tomography, computed tomography angiography or magnetic resonance imaging), neurological measurements (NIHSS score, mRS score), haematological examination (blood routine, blood glucose, hepatic and renal function, coagulation routine, urine routine, electrocardiogram, etc) and other information.  **Treatment period:** Intra-arterial administration of argatroban (0.2-0.3 mg/min), dexamethasone (0.1 mg/min) and edaravone (0.3 mg/min) for 30 to 60 minutes after the end of thrombectomy.  **Follow-up period:** NIHSS score will be assessed at 48±12 hours, and 10 ± 2 days after enrolment. At 48±12 hours, patients will receive brain computer tomography or magnetic resonance imaging. The mRS score will be assessed at 90 ± 7 days. All concomitant medications, adverse events, stroke recurrence and other vascular events of each visit are recorded since the last visit.  All the adverse events of included subjects should be recorded and tracked until properly resolved.  All the serious adverse events of included subjects should be recorded and tracked, even if the subjects have finished the trial, until the events are resolved, or stabilization judged by the investigator. |
| **Planed Duration** | 24 months |

**1.Background and current state of knowledge**

Acute ischemic stroke (AIS) accounts for approximately 85% of all stroke events and is one of the leading causes of morbidity and mortality worldwide, especially in patients with large vessel occlusion (LVO) [1,2] Currently, rapid recanalization of occluded arterial vessels by endovascular treatment (EVT) has been the most effective treatments in this population [3]. A harsh truth was that only 46.0% patients achieved functional independence although there was about 80% successful recanalization of LVO [3]. The reasons for this phenomenon are generally attributed to the re-occlusion of the vessel, haemorrhagic transformation after EVT and no re-flow in the cerebral microcirculation [4]. Among these reasons, this no re-flow phenomenon may be a major contributor to the poor prognosis. Previous studies have shown that the mechanisms underlying no-reflow are multiple, including endothelial swelling, pericyte constriction, microthrombus formation, neuroinflammation, oxidative stress, and disruption of the blood-brain barrier [5-10].

Based on the above discussion, we argue that intra-arterial treatments of argatroban, edaravone, and glucocorticoids may safely improve clinical outcomes in AIS-LVO patients with successful recanalization who received EVT given their multiple actions. For example, argatroban could prevent and reduce microthrombus formation; edaravone would scavenge free radicals; and glucocorticoids could inhibit neuroinflammatory response and reduce endothelial oedema. In this context, this trial is designed to explore the safety, feasibility and possible efficacy of sufficient endovascular recanalization bridged by intra-arterial cocktail therapy in this population.

**2.Objectives of the trial**

**2.1 Hypothesis tested**

This study intends to demonstrate that intra-arterial cocktail therapy could safely treat anterior circulation AIS-LCO patients with sufficient endovascular recanalization.

**2.2 Primary objective**

To test the hypothesis that intra-arterial cocktail therapy can safely improve favourable functional outcome at 90 days in anterior circulation AIS-LCO patients with sufficient endovascular recanalization.

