**8. Statistics**

**8.1 Sample size**

Given that this was a pilot, single-arm study, no formal sample size calculation was performed. A total of 30 patients was set based on the recommendation of the Steering Committee.

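### Sections 2.1 and 2.2 promise to demonstrate safety and test improvement, but a 30-patient single arm with no defined comparator, reference rate or haemorrhage bound can only estimate

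*Protocol*

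**What the plan says.** The protocol describes the purpose of the trial in two ways.

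- **Confirmatory wording.** Section 2.1: "This study intends to demonstrate that intra-arterial cocktail therapy could safely treat anterior circulation AIS-LCO patients with sufficient endovascular recanalization". Section 2.2: "To test the hypothesis that intra-arterial cocktail therapy can safely improve favourable functional outcome at 90 days".
- **Exploratory wording.** Abstract, Objective row: "To explore the safety, feasibility and efficacy of thrombectomy with sufficient recanalization bridged by intra-arterial cocktail therapy". Section 1: "this trial is designed to explore the safety, feasibility and possible efficacy".

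The title and section 3.1 describe a single-arm, single-centre pilot, and section 5.1 gives every enrolled patient the study drugs. Section 8.1 says that no formal calculation was made and adds: "A total of 30 patients was set based on the recommendation of the Steering Committee". The primary outcome (6.1) is the proportion with mRS 0-2 at 90 days, and the safety outcome (6.3) is sICH within 48±12 hours. Neither section gives a value against which the result is to be judged.

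Section 8.2 plans comparisons between two groups: logistic regression for 90-day mRS and sICH, 1:1 propensity score matching, and inverse probability weighting, all at two-sided P<0.05. No other section mentions a second group.

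**The concern.** A claim that a therapy improves an outcome needs something to improve on: a concurrent control, a described external control, or a fixed reference rate. A claim that safety has been demonstrated needs a rate of harm that the data must exclude. Sections 2.1 and 2.2 make both claims, and the protocol fixes none of these. Section 8.2 looks as if it fills the gap, but its comparator has no source, period, eligibility or size.

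What is at stake is what the trial may conclude. With a hypothesis on record but no criterion for it, a favourable-looking proportion or a low haemorrhage count could be reported as support for that hypothesis, and nothing in the protocol would say otherwise. If a control group is chosen after the 30 outcomes are known, its choice can shape the answer, and the P<0.05 rule would lend that comparison more weight than it can bear.

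**Working it through.** **1. The plan's own figure.** N = 30 comes with no event rate, effect size or power, so there is nothing to reproduce. What can be worked out is what 30 patients deliver.

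**2. Are the hypotheses testable as written?**

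| Needed | Where it would stand | What is there |
|---|---|---|
| Comparator or reference rate for mRS 0-2 | 2.2, 6.1, 8.1 | None |
| sICH rate to be excluded | 2.1, 2.4, 6.3, 8.1 | None |
| Second group for the tests | 3.1, 3.2, 5.1, 8.2 | Named in 8.2, defined nowhere |

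No null hypothesis can be written down for either claim.

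**3. Precision for sICH.** Input: n = 30 (8.1). Exact (Clopper-Pearson) two-sided 95% limits are

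- lower = Beta quantile(0.025; x, n − x + 1)
- upper = Beta quantile(0.975; x + 1, n − x)

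For x = 0 the upper limit reduces to 1 − 0.025^(1/30) = 0.116.

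| sICH events | Upper 95% limit |
|---|---|
| 0/30 | 11.6% |
| 1/30 | 17.2% |
| 2/30 | 22.1% |

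The chance of seeing no event is (1 − p)^30. For an assumed true rate of 5% it is 0.95^30 = 0.21, and for 10% it is 0.90^30 = 0.04. A clean result is thus weak evidence against a rate of 5%, and only moderately informative about 10%.

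**4. Precision for mRS 0-2.** Same formula, n = 30.

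| Count | Observed | Exact 95% interval |
|---|---|---|
| 14/30 | 46.7% | 28.3% to 65.7% |
| 15/30 | 50.0% | 31.3% to 68.7% |
| 18/30 | 60.0% | 40.6% to 77.3% |

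At 15/30 the half-width is (68.7 − 31.3)/2 = 18.7, or about ±19 points.

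**5. What 8.2 could deliver if its comparator were defined.** Matching 1:1 yields at most 30 pairs. Assume 50% with mRS 0-2 in each group and treat the groups as independent. The large-sample 95% half-width for the difference is 1.96 × √(2 × 0.5 × 0.5 / 30) = 1.96 × 0.129 = 0.253, or about ±25 points. Fewer matched pairs would widen it. Defining the comparator would make the test meaningful but would not make it confirmatory.

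**The case against.** The strongest reply is that the authors do plan a comparison. Section 8.2 names models, covariates, a caliper and a significance level, so section 2.2 can be read as resting on a control group the authors had in mind. This stands to the extent that it would be wrong to say no comparison is planned. It does not rescue the objective, because the group cannot be identified from the protocol. It does mean that rewording section 2 alone would leave 8.2 promising tests that the objectives no longer call for.

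A second reply is that this is loose phrasing in two sentences. Sections 2.3 and 2.4 are worded descriptively, the title says pilot, and 8.1 is open about the missing calculation. All of that is true, and a pilot needs no formal sample size calculation. But 2.2 is the primary objective, and the P<0.05 rule in 8.2 treats it as something to be tested.

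Two stronger readings are tempting and are not supported.

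- A reader might infer that the trial will be judged against the figure in section 1, "only 46.0% patients achieved functional independence although there was about 80% successful recanalization of LVO", and that enrolling only recanalized patients builds in an apparent gain. The protocol gives that figure once, as motivation, and ties it to no objective, endpoint or sample size. The size of any such gain would rest on an assumed outcome rate in non-recanalized patients and on equal case mix, and the documents give neither.
- A reader might infer that the result will decide whether a randomised trial goes ahead. The protocol describes no such decision and no follow-on trial.

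**Conclusion.** The point holds as an internal contradiction that affects what may be concluded. Sections 2.1 and 2.2 state confirmatory aims. The abstract, section 1, section 3.1 and section 8.1 describe an exploratory single-arm pilot, and 8.2 supplies no usable comparator. Neither hypothesis can be tested as written.

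What the design can give is two estimates: an sICH rate with an upper limit of 11.6% at best, and a proportion with mRS 0-2 known to about ±19 points near 50%. These limits assume 30 patients with complete outcome data; losses would widen them. The finding does not depend on any benchmark rate, and it is not a criticism of the number 30 or of the lack of a formal calculation. The change should be made before the results are reported.

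**What to change.** 1. **Sections 2.1 and 2.2.** Replace the hypothesis and the primary objective with estimation aims: the sICH rate within 48±12 hours and the proportion with mRS 0-2 at 90 days, each with an exact 95% confidence interval. This brings them into line with the abstract and section 1.
2. **Section 8.1.** Keep N = 30 and the statement that no formal calculation was made. Add the precision: upper limit 11.6% if no sICH is seen, and 31.3% to 68.7% at 15/30 with mRS 0-2.
3. **Limits of the claim.** State that the single-arm data will support no claim of improvement or of demonstrated safety.
4. **Section 8.2.** Reconcile it in the same amendment. Either remove the between-group tests, matching and weighting, or define the external comparator in advance (source, calendar period, eligibility) and label the comparison exploratory.

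No extra patients or visits are needed. The cost is a more modest claim and a revised 8.2. If the comparison is kept, there is also the work of specifying the control group before the outcomes are compared.

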**2.3 Secondary objectives**

1. To determine the proportion of excellent functional outcome at 90 days.
2. To determine occurrence of early neurological improvement within 48 hours.

**2.4 Safety objectives**

1. To determine occurrence of symptomatic intracranial haemorrhage.

**3. Design and selection of patients**

**3.1 Trail plan**

This is a prospective, pilot, single-arm, open label, blinded endpoint, and single centre trial.

All enrolled patients will receive intra-arterial administration of argatroban (0.2-0.3 mg/min), dexamethasone (0.1 mg/min) and edaravone (0.3 mg/min) for 30 to 60 minutes after successful recanalization. In addition, all patients will receive standard medical care as per national stroke guidelines.

Follow-up will be performed at baseline, 48±12 hours, 10 ± 2 days, and 90 ± 7 days, respectively.

All clinical assessments including NIHSS and mRS will be evaluated by certified assessors according to a standardized procedure manual. The primary endpoint (mRS at 90 days) will be mainly evaluated, in person or by telephone interview (if in person interview is not possible), by one trained and certified staff.

**3.2 Selection criteria:**

**Inclusion criteria: in order to be eligible, the patients must meet all of the following criteria:**

1. Age ≥18 years.
2. Patients who presented with acute ischemic stroke and a large vessel occlusion in the anterior circulation and met the criteria of mechanical thrombectomy.
3. Sufficient recanalization (mTICI 2b-3) within 7 hours of stroke onset.
4. Signed informed consent.

**Exclusion criteria: in order to be included the patients must not have any of the following criteria:**

- - 1. Insufficient recanalization (mTICI < 2a) after endovascular treatment;
    2. Haemorrhagic stroke: cerebral haemorrhage, subarachnoid haemorrhage.
    3. Coagulation disorders, systematic haemorrhagic tendency, thrombocytopenia （ <100000/mm3）.
    4. Severe hepatic or renal dysfunction, increase in ALT or AST (more than 2 times of upper limit of normal value), increase in serum creatinine (more than 1.5 times of upper limit of normal value) or requiring dialysis.
    5. Severe uncontrolled hypertension (systolic blood pressure over 200mmHg or diastolic blood pressure over 110 mmHg).
    6. Patients with contraindication or allergic to any ingredient of drugs in our study.
    7. Patients not suitable for the study considered by researcher.

**Elimination criteria:**

1. Those who did not receive intra-arterial drugs after enrolment;

2. There is no laboratory examination record during the study;

3. Those who used other treatments that are prohibited and affect judgment of efficacy.

**Drop-out criteria:**

1. Subjects lost to follow-up and voluntarily requested to withdraw;

2. Due to any comorbidities, complications or special physiological changes, the subject is not suitable to continue the trial based on the investigator’s judgement;

3. Due to the disease deterioration, the subject is withdrawn from the trial based on the investigator’s judgement;

4. Poor compliance after enrolment.

**Suspension Criteria:**

Trial suspension means that the clinical trial has not finished as planned, and the trial is stopped in the middle period. The purpose of trial suspension is to protect the rights and interests of subjects, ensure the quality of the trial, and avoid unnecessary economic losses:

1. Proportion of serious adverse events during the trial is high than unexpected, and Data and Safety Monitoring Committee (DSMC) has the right to terminate the study unconditionally.

**3.3 Duration of participation for each subject:**

Each subject will be followed up in the trial for 3 months.

**3.4 Measures to reduce bias:**

Final follow-up will be done at 90 days, in person or by telephone, by the trained and certified assessors. Central adjudication of clinical and safety outcomes will be also done by assessors who are unaware of clinical details.

**4 Plan and conduct of the trial**

**4.1 Clinical trial flow chart**

| Period  Item | Screening | Treatment | Follow-up | | |
| --- | --- | --- | --- | --- | --- |
| Visit | 1 | 2 | 3 | 4 | 5 |
| Time | 0 day ^1^ | After the end of EVT | 48 ± 12 hours | 10 ± 2 days | 90 ± 7 days |
| Inclusion/Exclusion Criteria | x |  |  |  |  |
| Sign informed consent | x |  |  |  |  |
| Demographic characteristics^2^ | x |  |  |  |  |
| Medical history | x |  |  |  |  |
| Physical examination | x |  | x | x |  |
| Brain CT/MRI | x |  | x |  |  |
| TOAST classification |  |  |  | x |  |
| ECG（12 lead） | x |  |  |  |  |
| 24h ambulatory ECG ^3^ |  |  |  | x ^3^ |  |
| Blood routine ^4^ | x |  |  |  |  |
| Urine routine ^5^ | x |  |  |  |  |
| Blood biochemistry ^6^ | x |  |  |  |  |
| Coagulation routine ^7^ | x |  |  |  |  |
| NIHSS score | x |  | x | x |  |
| mRS score | x |  |  |  | x |
| Concomitant medication |  | x | x | x | x |
| Adverse events |  | x | x | x | x |
| Stroke recurrence and other vascular events ^8^ |  | x | x | x | x |

1. Day 0: limited to the period from the onset of stroke to the time before randomization;
2. Demographic characteristics: The age of the subjects is calculated based on the identification (ID) card information;
3. 24h ambulatory electrocardiogram: required to be completed within 10 days of admission;
4. Blood routine: including total number of red blood cells (RBC), total number of white blood cells (WBC), platelet count (PLT), haemoglobin (HGB). The results are measured within 24 hours before screening;
5. Urine routine: including urine red blood cells (NRBC), urine white blood cells (NWBC), urine protein (PRO), and urine sugar (GLU). The results are measured within 24 hours before screening;
6. Blood biochemistry: Hepatic function tests: alanine aminotransferase (ALT), aspartate aminotransferase (AST), total bilirubin (TBIL), direct bilirubin (DBIL); Renal function tests: serum urea nitrogen (BUN), Creatinine (Cr); Blood Glucose (GLU); Lipid, including total cholesterol (TC), triglycerides (TG), high density cholesterol (HDL), low density cholesterol (LDL). The results are measured within 24 hours before screening;
7. Coagulation examination: prothrombin time (PT), activated partial thromboplastin time (APTT), fibrinogen (FIB), thrombin time (TT). The results are measured within 24 hours before screening;
8. Stroke recurrence and other vascular events: occurrence of stroke recurrence and other vascular events within 90 days from randomization.

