**6.6 Study periods**

**Screening period:** On day 0 (baseline period), it is necessary to complete enrolment screening, and collect demographic characteristics, medical history (including history of hypertension, diabetes and drug treatment history), brain imaging (computer tomography, computed tomography angiography or magnetic resonance imaging), neurological measurements (NIHSS score, mRS score), hematological examination (blood routine, blood glucose, hepatic and renal function, coagulation routine, urine routine, electrocardiogram, etc) and other information.

**Treatment period:** All enrolled patients receive intra-arterial drugs. The perioperative data including time and dose of intra-arterial drugs, LVO recanalization time, mTICI grade, etc. will be recorded and cranial CT will be performed immediately after the procedure.

**Follow-up period:** NIHSS score will be assessed at 48±12 hours, and 10 ± 2 days. Repeated brain CT will be performed at 48±12 hours. The mRS score will be assessed at 90 ± 7 days. All concomitant medications, adverse events, stroke recurrence and other vascular events of each visit will be recorded since the last visit.

All the adverse events of included subjects should be recorded and tracked until properly resolved.

All the serious adverse events of included subjects should be recorded and tracked, even if the subjects have finished the trial, until the events are resolved, or stabilization judged by the investigator.

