**7. Description of safety assessment parameters**

**7.1 Evaluate clinical safety:**

Physical examinations, including neurological assessments, imaging studies, will be performed at baseline, 48 ± 12 hours, 10 ± 2 days, and 90 ± 7 days after enrolment; adverse event of each visit will be collected after baseline visit.

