**Adverse events monitoring**

All information on adverse events, whether mentioned by subjects, discovered by investigators, or discovered through physical examination, laboratory tests, and other methods, should be recorded on the adverse events page of electronical case report form and handled in accordance with appropriate regulations and report.

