**Adverse Event (AE）**

The adverse event (AE) is any adverse medical event that occurs in a study subject during the course of a study that is not necessarily related to this treatment. Thus, the adverse event (AE) can be any unfavourable and unexpected sign (including abnormal laboratory findings), symptom or disease temporally related to the use of study treatments, regardless of whether it is related to the study treatments or not.

It is included that any events that are new or that have worsened in severity and frequency from baseline, including abnormal results from diagnostic methods such as laboratory tests.

Note: Adverse event collection begins with signed informed consent.

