**Abnormal laboratory test results**

During the course of the study, when the results of laboratory tests meet the following conditions, they must be regarded as adverse events and recorded in medical terms on the adverse events of the CRF:

1. Accompanying clinical symptoms
2. Causing a change in the trial protocol (eg treatment interruption or discontinuation)
3. Leading to a change in medical intervention or concomitant treatment
4. Clinically significant as judged by the investigator (medical and scientific methods should be used to judge whether an isolated laboratory abnormality is an adverse event)

When the adverse event meets the serious criteria, it should be reported in accordance with the serious adverse event reporting procedure.

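### No laboratory test is scheduled after the infusion, so silent laboratory abnormalities that the protocol counts as adverse events are recorded only where the ward happens to test

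*Protocol*

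**What the plan says.** Section 4.1 lists blood routine, urine routine, blood biochemistry and coagulation, each marked at Visit 1 only. Footnotes 4 to 7 time all four panels in the same way; for coagulation, "fibrinogen (FIB), thrombin time (TT). The results are measured within 24 hours before screening".

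The text on later visits names no laboratory test. Section 6.6 gives NIHSS, mRS, event recording and imaging ("Repeated brain CT will be performed at 48±12 hours"). Section 7.1 opens with "Physical examinations, including neurological assessments, imaging studies, will be performed at baseline" and goes on to the follow-up visits, again without laboratory tests.

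The safety sections nevertheless treat laboratory results as a source of adverse events:

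- Adverse events monitoring (7.1) covers events "discovered through physical examination, laboratory tests, and other methods".
- The adverse event definition covers new or worsened events, "including abnormal results from diagnostic methods such as laboratory tests".
- Abnormal laboratory test results (7.3) gives four conditions under which a result must be recorded as an adverse event. The fourth is clinical significance in the investigator's judgement, which includes deciding "whether an isolated laboratory abnormality is an adverse event".

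Two further places touch on laboratory data. An elimination criterion in 3.2 reads "There is no laboratory examination record during the study". Section 9.2 puts laboratory results in the list of source data to be verified, a list that ends by naming baseline and follow-up.

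**The concern.** The fourth condition in 7.3 needs no symptoms and no change of treatment, so it can be met only if someone has ordered a test. After the infusion the protocol orders none. A site that follows the chart exactly will have a planned baseline value for every patient and, afterwards, whatever the ward chose to measure.

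Safety is the first aim named in the Abstract, and all 30 patients are to receive argatroban, dexamethasone and edaravone intra-arterially. A symptom-free but important change in platelets, haemoglobin, creatinine, ALT/AST or glucose would be recorded in some patients and missed in others. A report of few or no laboratory adverse events could then reflect few abnormalities or few tests, and the data would not separate the two.

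**Working it through.** There is no stated figure to reproduce. The check compares the schedule with the recording rules.

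**1. What the chart orders after the infusion.** Take the two follow-up visits before day 90, at which patients may still be in hospital.

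| Row in 4.1 | Visit 3 (48±12 h) | Visit 4 (10±2 d) |
| --- | --- | --- |
| Physical examination | marked | marked |
| NIHSS | marked | marked |
| Brain CT/MRI | marked | – |
| Blood routine | – | – |
| Biochemistry | – | – |
| Coagulation | – | – |

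The three blood panels give 3 × 2 = 6 cells, of which 0 are marked. Visits 2 and 5 carry no laboratory mark either. Urine routine has the same pattern.

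**2. Whether the text fills the gap.** The Abstract's Procedure row, 6.6 and 7.1 were read for any test after treatment. None is named.

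**3. Which recording rules depend on a scheduled test.** The four conditions in 7.3 are:

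- *Condition 1, symptoms.* Examinations at 48±12 hours and 10±2 days would prompt a test. Largely covered.
- *Conditions 2 and 3, a change to the trial treatment or to other care.* The result has already been acted on, so a test exists. Covered.
- *Condition 4, clinical significance alone.* Nothing in the protocol prompts the test. Exposed.

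**4. Whether the other references set a test.** The elimination criterion gives no panel and no time after treatment, so the screening sample could satisfy it. Section 9.2 describes checking data that exist; it names no visit or panel. Sections 3.1 and 5.1 refer to guideline-based usual care without naming laboratory tests.

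**5. Size, as an illustration only.** Let q be the share of patients with a silent, clinically significant abnormality and c the share of those that usual care detects. Both are assumptions, because the documents give neither. With n = 30 and independent patients:

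- expected number recorded = 30 × q × c
- chance that at least one goes unrecorded = 1 − (1 − q(1 − c))^30

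| q | c | Expected to occur | Expected recorded | Chance at least one is missed |
| --- | --- | --- | --- | --- |
| 10% | 50% | 3.0 | 1.5 | 1 − 0.95^30 = 79% |
| 10% | 80% | 3.0 | 2.4 | 1 − 0.98^30 = 45% |
| 10% | 95% | 3.0 | 2.85 | 1 − 0.995^30 = 14% |
| 5% | 50% | 1.5 | 0.75 | 1 − 0.975^30 = 53% |
| 5% | 80% | 1.5 | 1.2 | 1 − 0.99^30 = 26% |
| 5% | 95% | 1.5 | 1.425 | 1 − 0.9975^30 = 7% |

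The last column runs from 7% to 79% on assumptions alone. It shows only that the answer turns on how completely the ward tests, which the protocol leaves open.

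**The case against.** The strongest reply is that nothing is contradicted. The rules in 7.1 and 7.3 classify results that exist; they do not promise a test. Collecting laboratory adverse events from usual care is compatible with a screening-only schedule, and patients who have just had a thrombectomy are likely to have blood taken anyway. Section 9.2 can be read as expecting laboratory data at follow-up, and the elimination criterion as expecting in-study results. This stands in part: it is a gap between schedule and rules, not a flat contradiction. It does not close the gap, because neither place sets a test or a visit. In 9.2 the closing reference to baseline and follow-up may attach only to the neurological scores.

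A second reply is that an eligibility limit, such as "increase in serum creatinine (more than 1.5 times of upper limit of normal value) or requiring dialysis", does not oblige anyone to recheck the value after one infusion of 30 to 60 minutes. That is right. The limits for platelets, ALT/AST and creatinine show which values the protocol cares about, and no more.

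A third is that complete testing would still leave little certainty. Zero events in 30 patients has a one-sided 95% upper limit of 1 − 0.05^(1/30) = 9.5%, and there is no concurrent control. That also stands. Scheduled tests make recording uniform; they do not make 30 patients enough to show safety.

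A reader might also count all four laboratory rows across Visits 2 to 5 and report 0 of 16 cells marked. The count is correct but overstates the practical gap, since it includes urine, the treatment visit and the day-90 visit, whose final follow-up may be by telephone.

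**Conclusion.** The point holds as a limited gap in adverse event recording. The protocol counts silent, clinically significant laboratory abnormalities as adverse events but plans no test that would find them after the drugs are given, so their recording depends on ward practice.

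A reader might infer that the trial's safety outcome is compromised, or that harm will be missed. The documents support neither. The one declared safety outcome, symptomatic intracranial haemorrhage, rests on NIHSS and brain imaging, both scheduled at 48±12 hours. The mRS outcomes and early neurological improvement use no laboratory data. Nothing in the protocol gives a rate of silent abnormalities or names a laboratory toxicity of the three drugs. The size of the loss therefore cannot be established; if ward testing is near complete, it is small.

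The conclusion assumes only that the flow chart means what it shows and that no document outside the protocol fixes post-infusion tests. It is a cheap improvement worth making and no threat to the trial's main results.

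**What to change.** - **Visit 3 (48±12 hours):** mark blood routine, biochemistry (including glucose) and coagulation. Use the routine inpatient result where one exists in the window, and take one routine blood sample only where none does.
- **Visit 4 (10±2 days):** transcribe available inpatient results for the same panels, with no new sample required.
- **Footnotes 4, 6 and 7:** restrict the 24-hour pre-screening timing to the Visit 1 sample.

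Urine routine can stay as it is; no eligibility limit rests on it.

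The cost is extra CRF fields and at most one routine sample per patient, 30 × 1 = 30 in the trial, fewer where the ward has already tested. Endpoints, eligibility and sample size do not change. Two limits remain: a sample at 48 hours may miss a transient coagulation effect of a short infusion, and a single arm cannot attribute any change to the drugs.
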